### Study setting

This trial aims to enroll and randomize 50 participants who receive care at the UW Post-COVID Rehabilitation and Recovery Clinic within the state of Washington. This is a high-demand outpatient clinic housed within an AMC that has served over 2500 patients since opening in 2020. Assuming a 10% dropout rate, a total of 50 participants will yield 20 completers in each study condition. This sample size was selected to characterize the intervention’s feasibility, acceptability, appropriateness, and preliminary efficacy to inform intervention improvement. A sample size of 20 participants in each condition (accounting for attrition) is appropriate given the specificity of our qualitative research questions [25, 26]. Likewise, this sample size is appropriate for estimating the proportion of participants who rate the intervention as feasible, acceptable, and appropriate. The lower bound of the 95% CI will be above 60% if at least 17 out of 20 (85%) of intervention participants rate the intervention as feasible, acceptable, or appropriate (Supplemental Fig. 1), which is a conservative estimate given satisfaction ratings for similar rehabilitation interventions [27].

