### Randomization and procedures to minimize bias

Participants are randomized using a 1:1 randomization to treatment versus wait-list control condition system. When participants confirm availability for an upcoming clinic group schedule and are confirmed eligible following the re-assessment of Eligibility, participants are 1:1 randomized to either the treatment experimental condition or wait-list control condition. The order of randomization is determined by the order in which participants chronologically completed the re-assessment of eligibility. To minimize bias, the clinicians delivering the intervention are blinded to the research participation status of their group members, as some group members will be enrolled in the study while others will not be. In addition, the REDCap system automatically sends participants baseline and post-treatment/wait-list survey links, where the participant can directly enter their data. As a result, the potential for study staff biases to interfere with data collection is avoided.

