### Statistical analysis plan

An intent-to-treat (ITT) approach will be used for all quantitative analyses. If participants are missing data at the individual-item level of a multi-item scale, we will impute the missing data using the within-group mean scores for the scale; however, a score will not be imputed if the participant is missing ≥ 40% data in a scale.

First, we will compute descriptive statistics to characterize the sample in terms of demographic and condition-related factors. To assess the first study aim, we will calculate the means and standard deviations of the AIM, IAM, and FIM and quantify the proportion of participants who rate the intervention as feasible, acceptable, and appropriate (average score greater than 3). We will quantify adherence as the percentage of sessions attended out of six sessions. These statistics will be used to contextualize the qualitative results and help inform the extent of modifications necessary to improve the feasibility, acceptability, and appropriateness of the intervention for adults with long COVID.

The second study aim to examine intervention effects is exploratory. We will determine whether randomization was successful by using *t*-tests and chi-square tests to compare the intervention and wait-list groups on a variety of demographic and baseline outcome variables. Any variables that differ between the groups will be included as covariates in the subsequent regression models. After examining randomization, we will explore intervention effects. For the second aim, we will conduct linear regression to assess intervention effects on each outcome (nine models) and will covary for the baseline level of the outcome variable, intervention credibility/expectancy [23], age, sex, and race.

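### A test-based rule with no list, threshold or cap adds covariates to the nine exploratory regressions, so the model is not fixed until the data are seen

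*Protocol article*

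**What the plan says.** Under Statistical analysis plan, the protocol article calls the second aim exploratory and takes it in two steps.

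- Step one is a check on the allocation: "We will determine whether randomization was successful by using" t-tests and chi-square tests between the arms on "a variety of demographic and baseline outcome variables". The consequence follows: "Any variables that differ between the groups will be included as covariates in the subsequent regression models".
- Step two is a linear regression for each of nine outcomes. These models "will covary for the baseline level of the outcome variable, intervention credibility/expectancy [23], age, sex, and race".

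No significance level, closed list of candidates or limit on added terms is stated. Under Screening and baseline assessments, participants complete the baseline questionnaires after they have been randomized. On size, Study setting says "This trial aims to enroll and randomize 50 participants" and expects 20 completers per arm.

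**The concern.** The check cannot do what is asked of it. If allocation was random, a demographic difference between arms is chance whatever its p-value. For the self-reported baseline scores the reading is less clear still, because they are collected after allocation. A difference there may be chance, or it may reflect how people answer once they know they are in the group or on the wait-list. Neither tells the reader whether the allocation process was sound.

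As a way to choose covariates, the rule looks at the wrong property. A covariate earns its place by predicting the outcome. This rule admits variables because they happen to be imbalanced, and it ignores a prognostic variable whose imbalance falls short of significance.

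At stake is a model that nobody can write down before the data arrive. A chance difference on one variable also carries into all nine regressions.

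**Working it through.** **Sample size in the models.** The plan states: "Assuming a 10% dropout rate, a total of 50 participants will yield 20 completers in each study condition". Its own inputs give 50 × 0.90 / 2 = 22.5 per arm, or 45 in all. Twenty per arm implies 1 − 40/50 = 20% dropout. The stated figure does not reproduce, so I use 40 to 45 people.

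**Fixed load.** Intercept, arm and five covariates make at least 7 parameters. Assuming more race categories and more than one expectancy subscale, the count could reach 11. At N = 40 this leaves 40 − 7 = 33 down to 40 − 11 = 29 residual degrees of freedom before any covariate is selected.

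**Number of new candidates, k.** Table 1 lists nine outcome measures taken at baseline in both arms. In any one model its own baseline is already included, which leaves 9 − 1 = 8 if all are tested. Age, sex and race are also already included. Further demographic or condition variables are not listed, so I assume k from 8 to 15.

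**Chance of adding something.** The 5% level is assumed. With independent candidates and true null hypotheses, P(at least one) = 1 − 0.95^k, and the expected number is 0.05k.

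| k | Expected terms added | P(at least one) |
|---|---|---|
| 8 | 0.40 | 34% |
| 11 | 0.55 | 43% |
| 15 | 0.75 | 54% |

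At a 10% level with k = 15, 1 − 0.90^15 = 79%.

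**Cost of one selected variable.** With N = 40 a variable is selected when |t| exceeds 2.024 on 38 degrees of freedom. Its squared correlation with arm is then at least r² = t²/(t² + N − 2) = 4.10/(4.10 + 38) = 0.097. Taken alone, it inflates the variance of the arm effect by at least 1/(1 − 0.097) = 1.11, before any gain from explaining the outcome. At N = 45 the factor is 1.09. If the tests use all 50 people, it is 1.08.

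**What the tests miss.** With 25 per arm, a mean difference reaches p < 0.05 only above about 2.01 × √(2/25) = 0.57 SD.

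**Net effect.** A simulation used 8,000 runs per setting, N = 40, five fixed covariates and 14 further candidates, two of them prognostic. Candidates were selected at p < 0.05, with correlation 0.3 between variables. Power is for an arm effect of 0.6 against a residual SD of 0.7.

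| | With selection | Fixed model |
|---|---|---|
| Mean standard error of arm effect | 0.282 | 0.272 |
| Type I error | 4.6% | 5.1% |
| Power | 55.3% | 55.8% |

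Dropping selection lowers the mean standard error by (0.282 − 0.272)/0.282, about 3.5%. At least one variable was added in 44% of runs and three or more in about 6%; the largest number was 11 to 12. With correlation 0.6, at least one was added in 30% and three or more in 9%, and type I error was 5.2% either way.

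**The case against.** The strongest case on the other side is that the consequence is limited. The variable most likely to matter, the outcome's own baseline, is in every model whatever the tests show, as are age and sex. The aim is labelled exploratory, and the Discussion says the sample suits exploration rather than a fully powered evaluation. The primary feasibility, acceptability and appropriateness results are descriptive and untouched by the rule. All of this stands, and it keeps the point modest.

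Several stronger readings are tempting, but the documents do not support them:

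- A reader might infer that the covariates as a whole are chosen by testing. Five are prespecified; the tests govern only the additions.
- A reader might infer that the rule overloads the regressions. Most of the load, 7 to 11 parameters, comes from the fixed list. The rule adds less than one term on average at 5% with these k, although nothing caps it.
- A reader might infer that the confidence intervals or tests become invalid. Selection uses only arm and baseline data, and the simulation shows no inflation of type I error.
- A reader might say that every baseline test has a null hypothesis known to be true. That holds for demographics but not cleanly for self-reports given after allocation, and the percentages above assume it for all candidates.
- The 34% to 54% range is not a figure from the plan. The level, the number of candidates and independence are assumptions, and correlation between symptom scales lowers it.

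What the objection does not do is defend the rule. Exploratory status does not make a baseline test informative about randomization, and the simulation shows no gain in power in return for an unfixed model.

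**Conclusion.** The point holds in a limited form. The plan states the rule outright, so this is a weak method and not a detail left to a fuller document. Beyond five prespecified covariates, the nine exploratory models take in whatever differs at baseline from an unlisted pool, so they are not fixed in advance, and the check offered as evidence of successful randomization cannot provide it.

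The numerical harm is small on average: a loss of precision, with the validity of the tests intact. In a minority of trials several terms would enter at once. These sizes rest on reading a difference as p < 0.05, on the assumed pool, and on a simulation that treats all five fixed covariates as measured in both arms. The change is worth making chiefly because it costs almost nothing and leaves a model that can be stated beforehand.

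**What to change.** Under Statistical analysis plan:

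1. Delete the test-based check of randomization and the sentence that turns its results into covariates.
2. Describe baseline characteristics by arm without p-values.
3. Use one covariate set, fixed in advance, for all nine models: the outcome's own baseline, age, sex and race. Write down the grouping of race before outcome data are seen; collapsing sparse categories afterwards would bring back the same dependence on the data.
4. Show any further adjustment only as a labelled sensitivity analysis.

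Credibility/expectancy is left out of this set because Table 1 marks it as completed by intervention participants only, so it cannot serve as a covariate across arms. That is a separate point, as is the collection of baseline measures after allocation, which this change does not cure.

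With race in two groups, for example, each model has 6 parameters (intercept, arm, baseline, age, sex, race), leaving 40 − 6 = 34 residual degrees of freedom at N = 40.

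The cost is a change of wording and less analysis work; the article says the analysis has not yet been done. The downside is that a chance imbalance outside the fixed set is not adjusted for in the main model. The baseline table and the sensitivity analysis would let readers see it.

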**Methods:**

This pilot trial (*N* = 50) uses a pragmatic, randomized two-group parallel design set within the University of Washington Post-COVID Rehabilitation and Recovery Clinic. The self-management intervention is a 6-week, group-based telemedicine intervention that teaches evidence-based strategies to manage common symptoms and improve stress management as well as communication and self-advocacy. The comparator is a wait-list control. Participants complete self-report measures of the primary and secondary outcomes at baseline and post-treatment/wait-list. Primary outcomes include intervention feasibility, acceptability, and appropriateness. Secondary outcomes include Patient-Reported Outcomes Measurement Information System measures of fatigue, sleep disturbance, cognitive difficulties, self-efficacy, pain interference, depression and anxiety symptoms, and a measure of long COVID symptoms and impression of change. At post-intervention, intervention participants also complete a qualitative interview to inform intervention refinement. Quantitative data will be examined using descriptive and statistical analysis including *t*-tests and chi-square tests to compare the intervention and wait-list groups on secondary outcomes. Qualitative data will be analyzed using the rigorous and accelerated data reduction technique (RADaR).

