Last, the telemedicine delivery platform and group format for the self-management intervention are strengths aimed at promoting intervention reach, implementation, and maintenance in the current AMC setting as well as future adoption in other AMCs [42]. Telemedicine delivery has the potential to improve access to the intervention, particularly for patients facing barriers to in-person treatment such as geographical barriers to in-person treatment (e.g., living in rural areas), socioeconomic barriers (e.g., limited access to reliable transportation), and/or other barriers such as symptom severity (e.g., cognitive or mobility impairment), and social distancing recommendations and related fear of COVID-19 infection [13, 43, 44]. Since the COVID-19 pandemic, telemedicine has become more routine following its rapid increase due to alterations to Medicare restrictions and reimbursement of telemedicine services [44]. Additionally, the group format of the self-management intervention has been shown to promote social support and feelings of validation and to reduce isolation [45, 46]. Importantly, there is evidence that group-based video teleconference interventions produce similar outcomes to in-person group treatment [47].

Some potential limitations must be acknowledged. The study is being conducted within a single AMC, which could limit the generalizability of the findings (e.g., due to the limited patient demographics). The sample size is adequate for a mixed-methods examination of feasibility and acceptability outcomes and is appropriate for *exploration* of intervention efficacy rather than *evaluation* using fully powered statistical analysis. Last, prospective participants are identified through the wait-list for the existing telemedicine group self-management intervention. Thus, they are likely to be more amenable to the intervention and delivery format compared to patients who did not indicate interest in the group and/or declined a provider referral to the group.

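### The nine regressions ignore clustering from group delivery in the intervention arm, so standard errors are too small if group members' outcomes correlate; the 60% bound for 17 of 20 also assumes independence and has little slack

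*Protocol article*

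**What the plan says.** The Abstract describes the treatment: "The self-management intervention is a 6-week, group-based telemedicine intervention". It also says "The comparator is a wait-list control". Under Randomization and procedures to minimize bias, allocation is by individual: "participants are 1:1 randomized to either the treatment experimental condition or wait-list control condition". The same section notes that clinic groups are mixed: "some group members will be enrolled in the study while others will not be".

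For the second aim, the Statistical analysis plan states "we will conduct linear regression to assess intervention effects on each outcome (nine models"). The covariates are the baseline value of the outcome, credibility/expectancy, age, sex and race, plus any variable found to differ between arms at baseline. No group or therapist effect, mixed model or robust standard error is named.

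The Study setting section justifies the sample size by the precision of the feasibility, acceptability and appropriateness proportions: "The lower bound of the 95% CI will be above 60% if at least 17 out of 20 (85%) of intervention participants" give a favourable rating. It names no interval method, refers to a supplemental figure that is not shown, and does not mention clustering.

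**The concern.** Individual randomisation followed by group treatment in one arm only is a partially nested design. Intervention participants in the same clinic group share a psychologist, a set of peers and six sessions; wait-list participants share nothing comparable during the comparison period. The Discussion gives a reason to expect shared influence: "the group format of the self-management intervention has been shown to promote social support and feelings of validation". The primary outcomes are ratings of that shared experience, so correlation within groups is plausible there too.

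Two things are at stake. The confidence intervals and p-values of the nine models, which will be read as preliminary evidence of efficacy, would be too optimistic. The precision claimed for the primary proportions would hold only if ratings within a group were uncorrelated.

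**Working it through.** **Inputs from the article.** 20 completers per arm, 17 favourable ratings of 20 (0.85), a 95% interval, 1:1 allocation (Study setting; Randomization and procedures to minimize bias).

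**Assumptions, not in the article.** m, the number of study members per therapy group, and the ICC. For the regressions the ICC is the residual one, after covariates. I use m = 2 to 7 and ICC = 0.05 and 0.10, with smaller ICCs mentioned where they matter.

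**Step 1: the article's own figure.** The two-sided 95% lower bound for 17/20 under independence is 0.621 (Clopper-Pearson), 0.640 (Wilson), 0.611 (Wilson with continuity correction), 0.631 (Agresti-Coull), 0.651 (Jeffreys) or 0.694 (Wald). All exceed 0.60. For 16/20 the Clopper-Pearson and Wilson bounds are 0.563 and 0.584. The stated figure reproduces as an independent-binomial result.

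**Step 2: the regressions.** Only the intervention arm is clustered. Its variance is multiplied by the design effect, DEFF = 1 + (m − 1) × ICC. With equal arms, the true standard error divided by the naive one is √((DEFF + 1)/2), and the actual type I error of a nominal 5% test is about 2 × (1 − Φ(1.96 / ratio)).

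Example, m = 5 and ICC 0.10: DEFF = 1 + 4 × 0.10 = 1.40; ratio = √(2.40/2) = 1.095; 1.96/1.095 = 1.79; type I error ≈ 7.4%.

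| m | ICC | DEFF | SE ratio | Type I error |
|---|---|---|---|---|
| 2 | 0.05 | 1.05 | 1.012 | 5.3% |
| 2 | 0.10 | 1.10 | 1.025 | 5.6% |
| 4 | 0.05 | 1.15 | 1.037 | 5.9% |
| 4 | 0.10 | 1.30 | 1.072 | 6.8% |
| 5 | 0.05 | 1.20 | 1.049 | 6.2% |
| 5 | 0.10 | 1.40 | 1.095 | 7.4% |
| 7 | 0.05 | 1.30 | 1.072 | 6.8% |
| 7 | 0.10 | 1.60 | 1.140 | 8.6% |

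Simulating a clustered arm against an independent arm, with 5 groups of 4, 4 of 5 or 3 of 7, agrees: about 6-7% at ICC 0.05 and 7-9% at ICC 0.10. At ICC 0.01 and m = 5 the standard error is only 1% too small (type I error about 5.2%).

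**Step 3: the 17/20 bound with clustering.** The effective sample size is 20/DEFF, and the interval is recomputed at 0.85 × 20/DEFF out of 20/DEFF.

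| m | ICC | Effective n | Clopper-Pearson | Wilson |
|---|---|---|---|---|
| 2 | 0.10 | 18.2 | 0.607 | 0.628 |
| 4 | 0.05 | 17.4 | 0.600 | 0.622 |
| 5 | 0.05 | 16.7 | 0.593 | 0.617 |
| 5 | 0.10 | 14.3 | 0.567 | 0.595 |
| 7 | 0.10 | 12.5 | 0.543 | 0.576 |

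The bound reaches 0.60 at DEFF 1.15 (Clopper-Pearson), 1.26 (Agresti-Coull), 1.36 (Wilson) or 1.49 (Jeffreys). At m = 5, where ICC = (DEFF − 1)/4, these correspond to ICCs of 0.038, 0.064, 0.089 and 0.123. At ICC 0.01 the bound stays above 0.60 for every m up to 10 (Clopper-Pearson 0.608 at m = 10).

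**The case against.** The strongest reply is that little depends on this. The article calls the second aim exploratory, and says in its limitations that the sample suits exploration rather than fully powered evaluation. The primary proportions are descriptive and no progression rule uses 60%. Groups also contain patients outside the study, so the number of study members per group may be small, and with 2 per group the effect is negligible. All of this stands and limits the severity. It does not make the stated model right: an exploratory interval should still have the width the design implies.

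Three stronger readings are tempting, and the article does not support them.

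- A reader might infer that the 60% bound is wrong, or that it fails under modest clustering. It is correct as a binomial statement. Whether it fails depends on m, the ICC and the interval method, none of which the article text gives. At 5 per group and ICC 0.05 it falls below 60% by Clopper-Pearson (0.593) but not by Wilson (0.617), Agresti-Coull (0.606) or Jeffreys (0.629).
- A reader might expect this trial's ICC to size the next one. It cannot. With 4 groups of 5 and an estimate of 0.05, the F-based 95% interval is about −0.16 to 0.77. At a true ICC of 0.05 the estimate is zero or negative in roughly half of such trials.
- A reader might infer that group membership is not being recorded. The article does not say, and a condensed article may leave that detail out.

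**Conclusion.** The concern holds for the regressions. The article fixes an independence model for a design in which one arm is clustered by delivery, and the error runs one way: with positive within-group correlation the intervention-effect standard errors are too small. At 4 to 7 study members per group, type I error is about 6-7% at ICC 0.05 and 7-9% at ICC 0.10, with standard errors about 4% to 14% larger than the naive ones. It is close to nominal at 2 per group or ICC 0.01.

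For the 17/20 statement the conclusion is conditional. The figure is right under independence, but that assumption is unstated and the margin is thin: 5 per group with ICC 0.10 takes both the Clopper-Pearson and the Wilson bound below 60%.

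These sizes rest on assumed group sizes and ICCs. The consequence is moderate; the point is worth acting on because correcting a stated model is cheap.

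**What to change.** - Fit the nine models as partially nested models: a random intercept for therapy group in the intervention arm only, wait-list participants as singletons, and Satterthwaite or Kenward-Roger degrees of freedom.
- State that the 17/20 bound assumes independent ratings, name the interval method, and show the bound over a range of group sizes and ICCs.
- Report the ICC with its interval as a descriptive result, with a warning that it is too imprecise to size a later trial.

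The change needs no alteration to design or recruitment, only group membership in the analysis data. The cost is somewhat wider intervals and few degrees of freedom. With few groups the variance component will often be estimated at zero, in which case the fit is essentially the ordinary regression; the report should say so where it happens and not present it as evidence that there is no clustering.

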** Secondary outcomes**			
Depression Short Form 8b** [21]		X	X
Anxiety Short Form 8a** [21]		X	X
Fatigue Short Form 8a** [21]		X	X
Sleep Disturbance Short Form 8a** [21]		X	X
Cognitive Function — Abilities Short Form 8a** [21]		X	X
Self-Efficacy for Managing Chronic Conditions — Managing Symptoms Short Form 8a** [21]		X	X
Ability to Participate in Social Roles and Activities Short Form 8a** [21]		X	X
Pain Interference Short Form 8a** [21]		X	X
Long COVID symptom and impact tools [22]		X	X
Credibility/expectancy questionnaire [23]		X*	
Patient Global Impression of Change scale [24]			X*

^*^Completed by intervention participants only

**Patient-Reported Outcomes Measurement Information System (PROMIS)

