### Screening and baseline assessments

The study coordinator provides a brief description of the study to prospective participants over the phone. Prospective participants who are interested in enrolling in the study are then screened for eligibility (see inclusion/exclusion criteria above). Eligible prospective participants complete the informed consent process to enroll into the study. Following enrollment, participants are asked to confirm their availability for upcoming self-management groups which are scheduled based on provider availability. If participants are available for the upcoming group schedule, participants complete a brief reassessment of eligibility, confirming that they have not participated in any other similar self-management programs targeting post-COVID symptoms. Within 2 weeks of the group’s Session 1 date, participants are randomly assigned to the intervention group or the wait-list control group. If availability is not confirmed, the study coordinator contacts the participants to confirm availability for the next group(s), as soon as that schedule is available from the clinic. Following randomization, participants complete a battery of self-report baseline measures. See Table 1 for study schedule and outcome measures. Study data are collected and managed using REDCap electronic data capture tools hosted at the UW [29, 30].

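### All nine exploratory between-arm regressions adjust for a credibility/expectancy score that only the intervention arm provides, so their arm effect cannot be estimated as written

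*Protocol article*

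**What the plan says.** For aim 2, the Statistical analysis plan section of the protocol article states: "we will conduct linear regression to assess intervention effects on each outcome (nine models"). The same sentence lists the adjustment: the investigators "will covary for the baseline level of the outcome variable, intervention credibility/expectancy [23], age, sex, and race". The section opens with a general rule: "An intent-to-treat (ITT) approach will be used for all quantitative analyses".

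Table 1 lists the credibility/expectancy questionnaire among the secondary outcomes. It has one entry, in the allocation column, and that entry carries a single asterisk. The footnote to the single asterisk reads "Completed by intervention participants only". The Patient Global Impression of Change row carries the same mark.

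The only missing-data rule in the article concerns single items within a scale. It fills them from within-group means, with a limit: "a score will not be imputed if the participant is missing ≥ 40% data in a scale".

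On timing, the section on screening and baseline assessments says: "Following randomization, participants complete a battery of self-report baseline measures".

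**The concern.** The regressions are meant to compare the two arms, and one of their covariates exists in only one arm. This is not a detail left for a fuller document. The article itself fixes both the covariate and its one-arm collection, and nowhere reconciles them.

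At stake is the only adjusted analysis that the article specifies for preliminary efficacy. As worded, it either gives no arm effect or needs a value for the wait-list arm that the article does not supply. In the second case the estimate and its standard error both depend on that value.

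**Working it through.** **Inputs from the article**
- Sample size: "This trial aims to enroll and randomize 50 participants" (Study setting).
- Allocation 1:1, so 50 / 2 = 25 per arm. The section on data collection gives the same 25 for the intervention arm.
- Expected completers: 20 per arm (Study setting).
- Covariates: baseline outcome, credibility/expectancy, age, sex, race.

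**Reproducing the count of nine.** Table 1 has 8 PROMIS short forms and 1 long COVID symptom and impact measure collected in both arms at both times: 8 + 1 = 9. The prose list of secondary outcomes could also reach nine, by counting 7 PROMIS domains, the long COVID measure and the Patient Global Impression of Change. That last scale, however, has no baseline and no wait-list data. On either count, credibility/expectancy is in every model.

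**Does the imputation rule help?** A wait-list participant lacks 100% of the scale, and 100% is at least 40%, so no score is imputed. There is also no wait-list group mean to impute from.

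**Complete-case fit.** The columns are intercept, arm, baseline outcome, credibility/expectancy, age, sex and race: 7 with race coded as binary. Dropping rows without a credibility/expectancy score leaves 25 rows at most, or 20 if only the expected completers contribute. All are intervention rows, so arm = 1 throughout and repeats the intercept. The rank is 7 - 1 = 6. This was confirmed in simulated data at 20 and at 25 per arm, in every one of 1,000 runs each. More race categories or extra covariates add columns but leave the deficiency of one.

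**Filling in a constant c for the wait-list arm.** Let m be the intervention-arm mean score, b the slope of outcome on score, and d the true arm effect. The arm coefficient then estimates the effect at score c:

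estimate ≈ d + b × (c - m)

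SE² ≈ SE₀² + (m - c)² × SE(b)², where SE₀ is the SE without the covariate.

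The article gives none of these values. Assume d = -0.40 SD, m = 6, score SD 1.5, b = -0.15 per point and 20 per arm. Simulation with 3,000 trials per setting gives:

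| Wait-list value | Formula | Simulated estimate | SE |
|---|---|---|---|
| covariate left out | -0.40 | -0.40 | 0.27 |
| intervention-arm mean | -0.40 | -0.39 | 0.27 |
| 5 | -0.40 + 0.15 × 1 = -0.25 | -0.25 | 0.30 |
| 3 | -0.40 + 0.15 × 3 = +0.05 | +0.06 | 0.48 |
| 0 | -0.40 + 0.15 × 6 = +0.50 | +0.48 | 0.85 |

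The shift depends on the assumed slope. In a second set of 3,000 trials per setting, filling with 0 gave -0.42 at slope 0, -0.10 at -0.05 and +0.19 at -0.10. The SE inflation does not need a slope: at slope 0 the SE was still 0.87, and 0.87 / 0.27 is about 3.2.

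**After removing the covariate.** The matrix has 6 columns and rank 6 and uses both arms (40 to 50 participants). In a separate simulation with a true effect of -0.50, the mean estimate was -0.50, with SE 0.27 at 20 per arm and 0.24 at 25 per arm.

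**The case against.** **The analysis is exploratory.** The article says so, and its discussion of limitations distinguishes exploration from a fully powered evaluation. The primary outcomes, the attendance measure and the qualitative aim do not use this covariate. All of that stands and limits the consequence. It does not help the nine models, since an exploratory model must still be fittable.

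**Aim 2 is not lost.** A reader might infer that preliminary efficacy cannot be examined at all. The article does not support that: the abstract also plans t-tests and chi-square tests of the two groups on secondary outcomes, and these need no covariate. The problem is confined to the regressions.

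**A reversed sign is not what the plan implies.** A reader might infer from the last row of the table that the plan would turn a benefit into a harm. The article never mentions filling with zero, and under the assumed distribution zero lies 6 / 1.5 = 4 SD below the mean. Filling with the intervention-arm mean does essentially no harm. What remains is that the article names no value. Nor does it show that a value would be picked after the data are seen.

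**Table 1 could be the passage in error.** The control condition is delayed treatment, so wait-list participants could have been asked about their expectations. The article does not settle this, and the authors need to say which passage reflects actual collection. Even then the score follows randomization. Whether participants know their arm when they answer is not stated; giving the questionnaire to one arm makes it likely, but no more than that.

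**Conclusion.** The concern holds for the nine aim 2 regressions as written. With the covariate collected as Table 1 says, a complete-case fit retains 20 to 25 intervention participants and no controls, and the arm effect is not estimable in any of the nine. This rests on the article alone and needs no assumed figures. It also conflicts with the intent-to-treat approach that the section announces, because a whole arm drops out.

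The size of the distortion under a filled-in value is illustrative. The range from about -0.40 (SE 0.27) to about +0.48 (SE about 0.85) depends on the assumed mean, SD, slope and 20 per arm, and its upper end on an extreme choice. It shows that the result would hang on an unstated decision; it does not predict what the trial will report.

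**What to change.** Delete credibility/expectancy from the covariate list of the nine between-arm models, keeping baseline outcome, age, sex and race. State that the score will be summarised for the intervention arm, or examined there as a predictor of outcome, and will enter no between-arm model. This costs one sentence and needs no new data. The article reports that the analysis has not yet been carried out, so the change can still precede it.

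The authors should also confirm who completed the questionnaire. If both arms did, correct the asterisk in Table 1. The score should still stay out of the between-arm models, because the baseline battery follows randomization and answers may reflect allocation.

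A score collected before randomization would be a legitimate covariate, but it is not a realistic repair here. The Trial status section puts the start of recruitment in January 2023 and the expected end of treatment in January 2024, and the questionnaire cannot be given before randomization to people already randomized. It is an option for the next trial.
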